## Abstract

**Background:**

The prevalence of obesity in adults with intellectual disabilities has consistently been reported to be higher than the general population. Despite the negative impact of obesity on health, there is little evidence of the effectiveness of weight management interventions for adults with intellectual disabilities and obesity. Preliminary results from a single-stranded feasibility study of a multi-component weight management intervention specifically designed for adults with intellectual disabilities and obesity (TAKE 5) and that satisfied clinical recommendations reported that it was acceptable to adults with intellectual disabilities and their carers. This study aims to determine the feasibility of a full-scale clinical trial of TAKE 5.

**Methods:**

This study will follow a pilot randomised trial design. Sixty-six obese participants (body mass index (BMI) ≥30 kg/m^2^) will be randomly allocated to the TAKE 5 multi-component weight management intervention or a health education ‘active’ control intervention (Waist Winners Too (WWToo)). Both interventions will be delivered over a 12-month period. Participants’ anthropometric measures (body weight, BMI, waist circumference, percentage body fat); indicators of activity (levels of physical activity and sedentary behaviour) and well-being will be measured at three time points: baseline, 6 and 12 months. The researcher collecting outcome measures will be blind to study group allocation.

**Conclusions:**

The data from this study will generate pilot data on the acceptability of randomisation, attrition rates and the estimates of patient-centred outcomes of TAKE 5, which will help inform future research and the development of a full-scale randomised clinical trial.

**Trial registration:**

ISRCTN52903778.

## Background

Intellectual disability is defined as the ‘disability characterised by significant limitations both in intellectual functioning and in adaptive behaviour, which covers everyday social and practical skills. The disability originates before the age of 18 years [1]’. Individuals with intellectual disabilities have consistently been reported to have higher rates of obesity than the general population [2–6]. Obesity, defined as a body mass index (BMI) of 30 kg/m^2^ or greater, is known to have a negative impact on health, associated with chronic diseases such as cardiovascular disease [7], some cancers [8] and type II diabetes [9]. Being overweight or obese has shown to further exacerbate the health needs and already reduced life expectancy of adults with intellectual disabilities [10]. Despite the negative impact of obesity on health, there is a limited evidence base to inform the management of obesity in this population [11].

Clinical guidance on the management of obesity advocates that adults who are overweight or obese should aim for a clinically important, sustainable weight loss of 5%–10% of initial body weight [12, 13]. To achieve this multi-component weight management, interventions are recommended which include as follows:Dietary changes to create an energy deficit diet (EDD) of 2,510 kilojoules (kJ)/day (600 kilocalories (kcal/day).Support to increase physical activity levels and decrease inactivity.Incorporation of behaviour change strategies to facilitate dietary and activity changes.A weight maintenance phase encouraging sustained behaviour changes in healthy eating, increased physical activity and reduced sedentary behaviour.A minimum 12-month study period (including the intervention and follow up) to examine the efficacy of the intervention.

Multi-component interventions have been used in the general population to successfully support individuals to lose a clinically important weight [14]. However, there are no published randomised controlled trials of weight management interventions meeting clinical recommendations in adults with intellectual disabilities.

Prior to this study, a single-stranded feasibility study was carried out to examine the efficacy of TAKE 5; a multi-component weight management intervention specifically designed for adults with intellectual disabilities and obesity [15, 16]. TAKE 5 was developed in collaboration with National Health Service (NHS) Greater Glasgow & Clyde Weight Management Service (GCWMS) [14] and modelled on their multi-component intervention, which incorporates diet and activity advice underpinned by behaviour change approaches and based on clinical guidelines [12, 13]. Full results from the TAKE 5 feasibility study have been published previously [15, 16]. The feasibility study found that TAKE 5 was acceptable to adults with intellectual disabilities, and carers, and reported clinically important reductions in body weight which were comparable to those achieved in adults with no reported intellectual disability following the GCWMS multi-component intervention [17]. Furthermore, clinically important reductions in risk factors associated with chronic diseases, such as waist circumference and increased physical activity levels, were also observed [15, 16, 18].

This study will add to the limited evidence base of controlled trials which have examined the efficacy of weight management interventions for adults with intellectual disabilities by piloting an intervention meeting current UK clinical recommendations on weight management. This study will compare the effects of a multi-component weight management intervention, TAKE 5 with a health education control intervention which does not include quantitative dietary advice to generate an individualised energy deficit, Waist Winners Too (WWToo). The design and rationale of the study with detail on the components of both interventions will be reported in this protocol.

### Aim

The overall aim of this pilot randomised trial is to examine the feasibility of a full-scale clinical trial of the TAKE 5 multi-component weight management intervention in comparison with a health education control intervention.

The key research questions to determine the feasibility of a full-scale randomised clinical trial are the following:Can adults with intellectual disabilities and obesity be recruited to a randomised study of the TAKE 5 intervention versus a health education control intervention?What attrition rates are observed at 6 and 12 months post-randomisation?Are the patient centred outcome measures acceptable to the participants and can they be measured reliably to detect clinically important changes?What are the sample size requirements for a full-scale clinical trial powered at 90% to determine a clinically important difference in body weight?

## Methods

The study will be conducted in accordance with the ethical principles of the Declaration of Helsinki and consistent with the principles of Good Clinical Practice. Ethical approval has been received from the Scotland A Research Ethics committee. In accordance with the Adults with Incapacity (Scotland) Act 2000, a detailed protocol of consent was implemented. This included seeking consent from individuals with intellectual disabilities with the capacity to provide informed consent and seeking consent from the nearest relative or welfare guardian in circumstances where the individual was unable to provide informed consent. Written informed consent was obtained from all participants or nearest relative or welfare guardian. Participants will have the right to withdraw from the study at any time and to decline to take part in any particular aspect or measure. This will be explained to them whilst seeking consent and their on-going consent will be checked and assessed throughout the intervention.

### Design

This study is a single-centre, single-blind pilot randomised trial. It consists of two active intervention arms: TAKE 5 multi-component weight management intervention versus treatment as usual (TAU), health educational intervention, WWToo. TAU in most areas in the UK for adults with intellectual disabilities and obesity is inconsistent—ranging from no intervention to the WWToo health education approach. An ‘active’ control intervention is preferred to the traditional non-intervention control group as due to the health risks associated with obesity [19, 20]; the research group believe it to be unethical to offer participants to be randomised to the control group with no intervention, for a 12-month period. Sixty-six participants will be randomised to the study (33 to each treatment arm) for a 12-month period; a 6-month weight loss period (comprising of 9–12 sessions designed to take place between two and three weekly intervals) followed by a 6-month weight maintenance period (comprising of six sessions taking place once a month). If the participants have not lost a clinically relevant weight loss of 5% of initial body weight at the end of the weight loss period, they will be advised to continue on the weight loss plan for a further 3 months, followed by a condensed 3-month weight maintenance period, mirroring the procedures conducted by the GCWMS and allowing a 12-month ‘intervention period’ for all participants. The study design is illustrated in Figure 1.

**Figure 1 Fig1:**
[figure not shown]
**Study flow chart.**

### Study population

Participants will be invited to take part in the study if they meet the eligibility criteria presented in Table 1.

**Table 1 Tab1:** **Participant eligibility, inclusion and exclusion criteria**

Criteria	
Inclusion	
Intellectual disability	Any level of intellectual disability
Age	Adults ≥18 years old (there is no upper age limit, in keeping with the GCWMS and specialist intellectual disability health services in NHS GGC)
Weight status	BMI ≥30 kg/m^2^
Ambulatory	Ability to walk (with or without a walking aid) for 10 min at a time based on self/carer report
Diet	Not currently on a prescribed or restricted diet, e.g. for phenylketonuria or diabetes
Weight stability	No intentional weight loss >3 kg over the previous 3 months
Exclusion	
Genetic intellectual disability	Participants with Prader Willi syndrome, Cohen syndrome or Bardet-Biedl syndrome as they require specific support to lose weight
Research	Currently taking part in any other research study
Medication	Taking medication; either prescribed or over the counter, designed for weight loss
Pregnancy	Individuals who are pregnant will be excluded from the study and anyone who conceived during the study will be excluded.

### Recruitment

One aim of the proposed study is to examine recruitment and retention to a randomised trial design and inform recruitment strategies that could be used in the development of a full-scale, multi-centre trial. Therefore, this pilot randomised trial will use a multi-point recruitment strategy, involving primary health care services, specialist intellectual disability services, relevant voluntary organisations and care provider organisations. A record will be kept of the numbers of potential participants, and individuals consenting to participate in the study, identified from each of the recruitment points.

The research team will visit staff working in these settings to explain the study and ask if their organisation would be willing to support recruitment to the study. For those staff willing to support recruitment to the study, a supply of study information packs will be provided, comprising information about the study including an invitation for potential participants to participate. Staff will be invited to distribute these packs to service users who they think would fulfil the study inclusion criteria and potentially be willing to take part. Potential participants, who reply to the invitation to the study by post using the self-addressed envelope provided, will indicate whether they would like to meet the researcher to find out more about the study. The researcher (LH) will then contact participants to arrange a visit, at a convenient location to the participant, to discuss the study. Individuals recruited to the study may live together and/or be supported by the same family or paid carers. These factors could make it difficult to randomise people to the different treatment interventions of the study and lead to some contamination between treatments and clustering of outcomes. Cluster randomisation, stratified by (and therefore analysed with adjustment for) the number of individuals within a randomised cluster, level of intellectual disabilities and presence of Down Syndrome will account for the clustering of outcomes and minimise imbalance between study groups.

### Sample size

There is limited data from controlled trials of weight management involving adults with intellectual disabilities on which to base a sample size calculation. This study is designed to estimate recruitment and retention rates for a full-scale clinical trial; it is not powered to detect a difference between study groups. Sixty-six participants will be recruited (33 to each treatment arm). This will provide sufficient insight into recruitment and retention rates, which will have a 95% confidence interval of no more than ±10%. The sample size will allow for a possible attrition rate of 20%. This study also aims to determine likely variance of study outcomes in order to power a larger randomised trial; if 50 participants provide outcome data at 12 months, a 90% confidence interval for each variance estimate will have a width of approximately 70% of the estimate (i.e. −26% to +44%).

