### Physical activity

#### Phase 1—weight loss

Results from the single-stranded feasibility study of TAKE 5 reported that individuals with intellectual disabilities and obesity have very sedentary lifestyles and have low levels of physical activity spending an average of 13.1 (SD 16.2) min per day in moderate-to-vigorous-intensity physical activity [15]. The majority of physical activity recommendations advocate 30 min of moderate-to-vigorous physical activity on most days of the week [30, 31]. This may be unrealistic and unattainable for some individuals with intellectual disabilities. Therefore, consensus guidelines on physical interventions for beginners [32] will be adhered to, initially aiming to support participants to progressively increase regular participation in physical activity and reduce time spent being sedentary.

In each session, physical activity goals will be negotiated and set based on the individual’s current level of physical activity, physical ability and individual’s expressed preference, with the overall aim to gradually work towards current physical activity recommendations advocated for all adults.

Participants will be encouraged to reduce the time spent sedentary, i.e. watching TV, by accumulating bouts of physical activity over the course of the day. Current activity across three types of physical activity will be reviewed with each participant and carer:

Activity at home as a replacement for sedentary behaviour, e.g. housework and gardeningWalking—based on baseline average steps per day, individuals will be encouraged to set targets to progressively increase walking behaviour and use pedometers to monitor step countsSport and exercise—information will be given to each participant on local leisure facilities and clubs with disability accessible sports and exercise groups/classes.

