### Data analysis

The main analysis of the pilot study will include descriptive statistics of feasibility outcomes, including recruitment rates and the acceptability of randomisation (recorded from attrition rates). This analysis will help inform the development of a full-scale trial. Additional analysis of patient-centred outcomes will be carried out according to a detailed pre-specified statistical analysis plan. The primary efficacy analysis, change in body weight at the end of the intervention period (≈12 months) from baseline will use a linear regression (random effects) model to take into account clustering and will be adjusted for randomised group, baseline weight and variables used in the minimisation algorithm (level of intellectual disabilities and presence of Down Syndrome). Similar linear regression models will be fitted for each continuous secondary outcome measure. A logistic regression model will be fitted for the categorical outcome, weight loss of 5% or more of initial body weight taking account of clustering and baseline adjustments listed above. Further analyses may assess the effects of baseline characteristics on outcomes and investigate the evidence for interactions with treatment effects using regression models.

Analyses will be conducted according to the intention to treat (ITT) principle. Per-protocol analyses, including only those participants who engaged with the programme, will also be used to test the sensitivity of the ITT results. Analyses will initially be performed using only those individuals for whom outcome data are available. Participants, who are lost to follow-up, will be assessed to see if they were different at baseline to those included in these analyses. As this is a pilot trial, the level of missing data will be recorded, but no value imputation for outcome variables will be conducted.

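### The −26% to +44% interval promised for every variance estimate holds for near-normal outcomes such as weight, but not for moderate-to-vigorous activity

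*Protocol article*

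**What the plan says.** The Sample size section gives estimating variances as a second purpose of the pilot: "This study also aims to determine likely variance of study outcomes in order to power a larger randomised trial". It then fixes the expected precision, on the premise that 50 people have 12-month data: "a 90% confidence interval for each variance estimate will have a width of approximately 70% of the estimate", with limits of −26% and +44%. No distributional assumption is stated, and no outcome is excepted.

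The secondary outcomes include the percentage of time per day spent in moderate-to-vigorous activity (Secondary outcome). In the physical activity section for the weight loss phase, the protocol reports the feasibility-study level of that activity: "an average of 13.1 (SD 16.2) min per day in moderate-to-vigorous-intensity physical activity".

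On analysis, the Data analysis section says "Similar linear regression models will be fitted for each continuous secondary outcome measure", and refers to a separate statistical analysis plan for detail. On what the full trial is to be sized for, the Aim section asks "What are the sample size requirements for a full-scale clinical trial powered at 90% to determine a clinically important difference in body weight".

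**The concern.** A single precision figure is offered for every outcome, but the formula behind it depends on normality. Unlike an interval for a mean, an interval for a variance does not become robust to non-normality as the sample grows, because its error depends on the kurtosis of the data. The protocol's own figure for moderate-to-vigorous activity has an SD above its mean on a scale bounded at zero, so normality is not credible for that outcome.

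At stake is how far readers trust one of the pilot's intended products. Anyone who used the activity variance to plan later work, and took −26% to +44% as its uncertainty, would be seriously overconfident.

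**Working it through.** **Inputs.** From Sample size: 50 participants with 12-month data, a 90% interval, stated limits −26% and +44%. From the physical activity section: mean 13.1, SD 16.2 minutes per day. From Data analysis: a model with randomised group, baseline value, level of intellectual disability and Down syndrome. Assumed by me: the shape of the activity distribution, which the protocol does not give.

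**1. Reproducing the stated figure.** The normal-theory interval for a variance, relative to its estimate, runs from df/χ²(0.95; df) − 1 to df/χ²(0.05; df) − 1. With df = 50 − 1 = 49:
- lower: 49/66.34 − 1 = −26.1%
- upper: 49/33.93 − 1 = +44.4%
- width: 70.6%

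This matches the protocol, so the arithmetic is right and the basis is one independent normal sample of 50.

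**2. How much the one-sample basis matters for weight.**
- Pooling within two arms, df = 48: −26.3% to +45.0%, width 71.4%.
- Full model: intercept 1, group 1, baseline 1, four-level disability category 3 and Down syndrome 1 make 7 coefficients, so df = 50 − 7 = 43. Limits: 43/59.30 − 1 = −27.5% and 43/28.96 − 1 = +48.5%, width 75.9%.

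Both treat the 50 as independent. Clustering could widen the interval, but the protocol gives no intracluster correlation or cluster size from which to say by how much. On a figure labelled approximate, these shifts are small.

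**3. Is normality possible for moderate-to-vigorous activity?** SD/mean = 16.2/13.1 = 1.24. A normal distribution with these moments would put Φ(−13.1/16.2) = 20.9% of values below zero, which is impossible for minutes per day.

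**4. Coverage under skewed shapes with the same mean and SD.** Simulated samples of 50 (100,000 per shape), applying the 49-df interval each time:

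| Assumed shape | Coverage of nominal 90% interval | Sample variance as a share of the truth, 5th–95th percentile |
|---|---|---|
| Normal | 90% | 69% to 136% |
| Gamma | 54% | 43% to 189% |
| Lognormal | 33–34% | 27% to 253% |

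The gamma has shape (13.1/16.2)² = 0.654 and excess kurtosis 6/0.654 = 9.2. The effective degrees of freedom are then about 2/(2/49 + 9.18/50) = 8.9, which gives an interval of roughly −47% to +172% in place of −26% to +44%.

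**5. Does using baseline values rescue it?** For change scores built from correlated gamma values, coverage was 54% at a correlation of 0.5 and 38% at 0.8. For residuals after regression on baseline it was 54% and 41%. In these assumed models it does not.

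**6. Does a transformed scale help?** In the gamma model, the same interval for the variance of the transformed values covered about 86% on the square-root scale and 97% on log(x + 1).

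**The case against.** The strongest reply is that the figure is a correctly computed planning approximation, labelled as such, and that it is adequate for the outcome that matters. The Aim section sizes the full trial on body weight, and nothing in the protocol suggests that weight departs far from normality. That stands. A reader might infer that the full trial would be badly sized because of this. The documents do not support that, since activity variances are not the stated basis for its size.

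A second reply concerns the evidence. The 13.1 (SD 16.2) is a raw level in minutes per day from the feasibility study, whereas the trial outcome is a percentage of time, analysed with baseline adjustment. No figures are given for light activity, sedentary time, change scores or residuals. This stands as a limit on scope: the demonstration covers moderate-to-vigorous activity only, and the coverage figures depend on assumed shapes. It does not remove the point. Re-expressing minutes as a percentage does not by itself remove skew, and the checks on change scores and residuals did not restore coverage.

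A reader might also infer that prescribing linear models for a skewed outcome is an error in itself. The protocol does not support that reading either. A linear model concerns residuals, could be fitted on a transformed scale within the wording used, and its details are commonly left to the statistical analysis plan, which is cited but not shown. Nor does the protocol say that chi-square intervals will be reported for each outcome, so it cannot be said that the published intervals will be wrong.

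**Conclusion.** The precision statement is too broad. It holds approximately for near-normal outcomes such as weight, where allowing for the model's residual degrees of freedom moves it only from −26%/+44% to about −27%/+48%, clustering aside. It does not hold for moderate-to-vigorous activity, where a nominal 90% interval would cover the true variance about 54% of the time under a gamma shape and about 33% under a lognormal.

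The failure of normality follows from the protocol's own mean and SD for a non-negative quantity. The size of the shortfall rests on the assumed shapes and on the trial population resembling that of the feasibility study. Severity is minor: the recruitment target of 66 does not change, and neither does sizing the full trial on weight.

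**What to change.** In the Sample size section, limit the −26% to +44% statement to approximately normal outcomes such as body weight, and add that the precision of the activity variances will be much poorer. For moderate-to-vigorous activity, obtain the variance interval on a transformed scale (square root, or log with a small offset for zeros) or by a bootstrap that resamples clusters.

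The cost is a sentence or two in the protocol and a modest addition to the analysis. The drawbacks are a less direct scale for interpreting the activity variance and a less favourable stated precision. No extra participants and no design change are needed.
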